#### Participatory approach (PA)

The Participatory approach (PA) is coordinated by one of the independent RTW-coordinators. Participants will receive PA six weeks after baseline; after completing the e-Health program or after care-as-usual, depending on their respective condition. The RTW-coordinator plans three meetings: the first meeting with the employee, the second meeting with his or her supervisor and the third meeting with the employee and supervisor. These meetings are scheduled shortly after each other (e.g. within two weeks).

In the first meeting, the employee is guided by the RTW-coordinator to perform a task-analysis and obstacle inventory. In a guided conversation, the employee first lists their main responsibilities and activities in their work, and uses this list to identify obstacles for RTW. The first meeting finishes after ranking the obstacles for RTW based on priority, frequency and perceived severity. If the employee received e-Health they already practiced with this and they can use that list to refine obstacles together with the RTW-coordinator. At the second meeting, the task-analysis and obstacle inventory are performed from the perspective of the supervisor, together with the RTW-coordinator. In the third meeting, the employee and his or her supervisor discuss the identified obstacles and brainstorm about solutions for these obstacles. Under guidance of the RTW-coordinator, they will rank the solutions, based on feasibility, solving capability and short-term applicability. The third meeting concludes with a RTW plan. This RTW plan includes the chosen solutions based on consensus between the employee and the supervisor, and is formulated in terms of who is responsible, to do what and when. At the end of the meeting, the RTW-coordinator plans an evaluation moment with the employee and the supervisor. The chosen solutions are to be implemented in the weeks after the third meeting, ideally within a time frame of 3 months. After three months the actual implementation of the solutions will be evaluated by the RTW-coordinator, together with the employee and the supervisor.

### Outcome measures

#### Effect evaluation

The primary outcome measure is time to lasting RTW. Lasting RTW is defined as RTW to the employee’s previous position, or another position with equal earnings, for a minimum of four consecutive weeks. Time between the first day of absenteeism with psychological distress and lasting RTW is calculated in calendar days and will be based on self-report through monthly diaries that participants are asked to fill in online. In addition, permission was requested to obtain these data from the OHS.

The secondary outcome measures consist of (1) (severity of) stress-related symptoms, (2) total sick-leave days, (3) self-efficacy and (4) self-reported health. Stress-related symptoms are measured with the 4DSQ [19, 24]. This questionnaire consists of 50 items, with subscales distress, depression, anxiety, and somatization. The items are scored on occurrence in the past week on a 5-point Likert scale, ranging from “no complaints” to “very often/continuously”. The total number of sick-leave days is based on the same data as time to lasting RTW (self-report and/or absenteeism record). Self-efficacy with regard to RTW is measured using the Work Self-Efficacy questionnaire. This questionnaire consists of 11 items and is specifically designed to measure self-efficacy for RTW in employees with mental health problems [25]. Self-reported health is measured with the Patient Reported Outcomes Measurement Information System (PROMIS) questionnaire. The PROMIS covers three domains of reported health: physical, psychological and social aspects of wellbeing. [26].

#### Covariates

By means of questionnaires we will gather information on the following covariates: (1) sociodemographic data, (2) job characteristics, (3) psychosocial risk-factors, (4) behavioral determinants of RTW. Sociodemographic data will include age, sex as reported by the employee, educational level and household composition. Job characteristics include type of work and contractual hours. Psychosocial risk-factors will be measured using the Job Content Questionnaire (JCQ; [27]. This questionnaire is designed to measure the social and psychological characteristics of jobs, including psychological demands, decision latitude (the employees’ potential control over his tasks and conduct during the workday), social support, physical demands and job insecurity. Behavioral determinants of RTW following the ASE model consist of the employees’ attitude, social influence and self-efficacy [28, 29].

#### Data analysis

Descriptive statistics will be provided for all relevant variables at baseline. To investigate the effectiveness of the interventions of the stepped care approach on lasting RTW a cox-regression will be conducted. To determine the effect of e-Health separately, the group who received [e-Health and PA] will be combined with the [e-Health only] group, and compared to the control- and [PA only] group. The same logic applies to PA; the PA groups will be combined and compared to the control- and [e-Health only] group. To test whether the combination of e-Health and PA in a stepped-care approach is superior to the separate interventions alone, we will study the interaction between PA and e-Health. For the secondary outcomes, depending on the type of outcome measure (continuous/categorical) generalized linear models or mixed effects logistic regression will be used. Analyses are conducted both unadjusted and adjusted for potential confounders. Additionally, effect modification of several factors, such as the (severity of) stress-related symptoms and cognition towards RTW despite symptoms, will be investigated by using interaction terms.

All analyses will be performed according to the intention-to-treat principle (ITT), which implies that all employees are analyzed according to the group they were assigned to, regardless of whether they actually received the intervention.

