**Methods:**

RESTART is a randomized controlled trial with a 2 × 2 factorial design and a follow-up of one year. Employees eligible for this study are those who reported sick within 2 to 8 weeks with psychological distress based on a distress screener. Participants will be randomized to a group receiving a tailored e-Health app or usual care, as well as randomized to a group receiving a Participatory Approach (PA; conversational method) in the workplace or usual care. The PA will however only be provided in case of persistent sickness absence at 8 weeks. Measurements take place at baseline, after the e-Health intervention period (3 months), and after the PA intervention period (6 months) and 12 months. Primary outcome is lasting RTW, defined as full RTW in previous or equal work for at least four consecutive weeks. Secondary outcomes are (the severity of) stress-related symptoms, total number of sickness absence days, self-efficacy for RTW and self-reported health. A process evaluation including a realist evaluation will also be conducted.

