### Sample size

The sample size was calculated based on number of cases needed to identify an effect on time to (lasting) RTW. Based on previous research of RTW interventions for employees with psychological distress a hazard ratio (HR) was chosen of 1.8 [11, 12, 21]. A sample size calculation was performed with an HR of 1.8, alpha of 0.5 and power of 80%, which generated a total sample size of 144 participants, 36 participants per group. Accounting for a loss-to-follow up of 15% after 12 months, we aim to include 166 participants.

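### No single primary Cox model is fixed: the other randomised factor is unnamed, unadjusted and adjusted results rank equally, and the clock starts before randomisation (minor; improvement at no cost)

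*Protocol article*

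**What the plan says.** Three statements in the protocol article bear on this point.

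- **Model terms.** Data analysis announces a Cox regression for lasting return to work (RTW). For e-Health, "the group who received [e-Health and PA] will be combined with the [e-Health only] group, and compared to the control- and [PA only] group". The Participatory Approach (PA) is handled in the same way. The other factor is not named as a covariate or stratum, nor is it said to be left out. The same section plans a test of the interaction between the two interventions, and that model has to contain both.
- **Adjustment.** "Analyses are conducted both unadjusted and adjusted for potential confounders". Neither version is called primary. Covariates lists four broad families of variables and does not say which of them form the adjustment set.
- **Clock.** Under Effect evaluation, "Time between the first day of absenteeism with psychological distress and lasting RTW is calculated in calendar days". Study population admits people already absent for 2 to 8 weeks, and Randomization and blinding places both randomisations directly after baseline. Delayed entry is not mentioned.

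**The concern.** A Cox hazard ratio is non-collapsible. If a factor that affects the outcome is left out, the estimated HR for the remaining factor moves towards 1 and some power is lost, even with perfect balance. A trial that randomises two factors can avoid this by putting both in the model.

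Two unranked results for each main effect raise a different problem. With two factors there are four candidate hazard ratios for the primary outcome, and nothing says which carries the conclusion. Confounding is also a weak basis for choosing covariates in a randomised trial, where the reason to adjust is prognosis.

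The clock starts before anyone is under observation. A participant must still be absent at entry, so no event can occur in the first 14 to 56 days of that participant's measured time. Without delayed entry, the early risk sets hold people who could not yet have an event.

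**Working it through.** **Inputs from the documents.** Sample size: "a hazard ratio (HR) was chosen of 1.8", power 80%, and "a total sample size of 144 participants, 36 participants per group", hence 72 v 72 for each main effect. Follow-up is 12 months. The lag to entry is 14 to 56 days. PA starts six weeks after baseline.

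**Assumptions.** Two-sided alpha of 0.05 (the article prints 0.5, a separate matter). The article gives no event fraction, so a range is shown. Event times are exponential and the lag is uniform over 14 to 56 days.

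**Step 1: the plan's own figure.** With 1:1 allocation, the Schoenfeld formula gives events = 4(1.960 + 0.842)² / (ln 1.8)² = 4 × 7.849 / 0.3455 = 90.9, so 91. Freedman's formula gives (2.8/0.8)² × 7.849 = 96.1, so 97. Then 91/144 = 63% and 97/144 = 67%. The planned 144 therefore fits only if about 63 to 67% reach lasting RTW. Without a stated event fraction it can be neither confirmed nor refuted. The scenario with 66% events is the one closest to the plan.

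**Step 2: leaving out the other factor.** 8,000 simulated trials per row, 36 per arm, e-Health HR 1.8, clock from randomisation. Monte Carlo error is about 0.4 points.

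| PA HR | Events | Pooled: HR, power | Both factors: HR, power | Loss (points) |
|---|---|---|---|---|
| 1.8 | 66% | 1.77, 78.5% | 1.81, 81.0% | 2.5 |
| 1.8 | 86% | 1.75, 88.0% | 1.82, 90.5% | 2.5 |
| 1.8 | 95% | 1.74, 89.4% | 1.82, 92.6% | 3.2 |
| 1.4 | 61% | 1.81, 78.7% | 1.82, 79.4% | 0.7 |
| 1.0 | 55% | 1.81, 73.8% | 1.81, 74.0% | 0.2 |

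Stratifying by the other factor does the same job (HR 1.81, power 80.6% in the first row). If PA acts only after day 42 (4,000 trials), the loss is smaller. With PA HR 1.8 it is 79.6% v 81.4% at 67% events and 91.0% v 92.2% at 96%. With PA HR 1.4 it is 77.8% v 78.6% at 63% events.

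Type I error, with e-Health HR 1.0 and PA HR 1.8: 4.4% pooled, 4.9% with both factors.

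**Step 3: two unranked results.** 4,000 trials per row, both HRs 1.8, about 68% events, one baseline predictor of assumed strength. The pooled unadjusted model is compared with a model holding both factors and the predictor.

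| Log HR per SD (assumed) | Power, pooled unadjusted v fuller model | Disagree on significance |
|---|---|---|
| 0.2 | 78% v 82% | 7% |
| 0.3 | 78% v 83% | 9% |
| 0.5 | 72% v 82% | 15% |

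At 80% events and log HR 0.5, power is 76% v 88%. With PA HR 1.0 and log HR 0.3 it is 77% v 81%. Over all runs with log HR 0.3 to 0.5, the gain is about 3 to 13 points and disagreement about 6 to 15%. A separate run of 1,200 trials (67% events, log HR 0.5) splits the gain: 71.0% pooled, 73.8% with both factors, 80.8% with the predictor as well. Most of it comes from the predictor.

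**Step 4: the clock.** Pooled HR from randomisation v from the first sick day without delayed entry, both true HRs 1.8:

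- 66% events: 1.767 v 1.766
- 95% events: 1.741 v 1.735
- 99.6% events (control median 60 days): 1.746 v 1.721, a shift of 0.025, with power 90.7% v 89.5%

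In that last, extreme case the two-factor model shifts from 1.820 to 1.784. Delayed entry at randomisation removes the shift (1.750 pooled, 1.820 with both factors). Each reported time is longer by that participant's own lag of 14 to 56 days.

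**The case against.** The pooling sentence may be shorthand. Merged-arm contrasts are the usual way to describe a factorial analysis, the planned interaction needs both factors in a model, and an article often leaves exact terms to the analysis plan. That stands: omission of the other factor is a natural reading of the text, not a stated fact.

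The loss is also conditional. Background reports that a previously evaluated e-Health programme did not affect lasting RTW and that PA had no overall effect, so a weak second factor is plausible and the loss could be close to nil. Against this, the Discussion expects the combination to beat either intervention alone, so on the trial's own hypothesis the other factor matters.

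The gain from covariates rests on an assumed predictor strength that no figure in the article supports, and an adjusted analysis is already planned. Both remarks are right. What remains is that the adjusted result has no stated rank or variable set.

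Finally, duration from the first sick day is an openly stated definition applied equally to all arms, and absence before entry is a real part of it. That stands too. The reported times are not false, but part of each one lies before the interventions could act.

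**Conclusion.** The point holds as a minor one. The article states the equal rank of two results and the early clock. It leaves the place of the other factor unclear.

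The omitted factor costs about 2 to 3 points of power if its HR is 1.8, less if its effect is weaker or delayed, and nothing if it is null. The unranked results allow selection in roughly 6 to 15% of trials, given a predictor of log HR 0.3 to 0.5 per SD. The clock moves the pooled HR by at most about 0.025, and by almost nothing at the event fraction that 144 participants imply. These sizes rest on the assumed event fractions, constant hazards (a Weibull check gave the same pattern) and uniform lag.

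A reader might infer three stronger things that the documents do not support:

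- **That all three features attenuate the HR and lose power.** Naming no primary result does neither; it leaves a choice. The clock's effect is close to zero in most scenarios.
- **That the tests are invalid.** Rejection under the null stayed at or below 5%.
- **That days before randomisation enter the sick-leave total.** Effect evaluation says only that the total uses the same data source and gives no start date for the count.

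**What to change.** Name one primary Cox model, before the allocation codes are opened:

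- Include e-Health and PA together, or stratify each comparison by the other factor. The planned interaction is then one added term.
- Prespecify a short set of baseline covariates chosen for prognosis, for example baseline 4DSQ distress and days absent at baseline.
- Measure time from randomisation, or keep the first-sick-day scale with delayed entry at randomisation.
- Label the unadjusted pooled comparison a sensitivity analysis.

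The cost is wording only. The 4DSQ is already administered, and days absent at baseline follow from the first-absence date that the outcome definition requires. No extra participants or data are needed.

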### Randomization and blinding

Randomization takes place on employee level. In addition to usual care, participants can receive e-Health and/or PA. This leads to a 2 × 2 factorial design, which allows to test the main effects of e-Health and PA separately, as well as the combined effect on lasting RTW. Therefore, participants are randomized twice, which results in two comparisons in the main outcome analysis: PA vs. not PA and e-Health vs. no e-Health. On top of usual care participants receive either: (1) e-Health and PA, (2) e-Health only, or (3) PA only (see Fig. 1). A time schedule of enrolment, interventions, and assessments are presented in Fig. 2. Both randomizations take place directly after baseline to ensure even-sized groups. If, however, participants who are assigned to receiving PA (partially) returned to work before PA starts, they will not receive PA.

A computer-based randomization list, generated by an independent researcher, will be used to allocate participants, based on their participant-ID, to one of the four groups. Before the statistical analyses are performed the condition-IDs are recoded by an independent researcher, which allows the primary researcher to be blinded for the allocation and the RCT to be single-blind.

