## Discussion

In the RESTART study, we will evaluate the effectiveness of a stepped-care approach on lasting RTW for employees on sickness absence with psychological distress. We will examine the main effects as well as the combined effect of the e-Health and PA on time to lasting RTW. We hypothesize that the stepped-care approach, e-Health followed by PA, will be more effective on time to lasting RTW compared with usual care, and e-Health or PA only.

As has been shown in previous research, there are three identified key elements for successful lasting RTW for employees with psychological distress. These include an explicit focus on RTW and not only on reduction of symptoms, having a positive cognition towards RTW and involvement of the workplace environment [11, 12]. In the RESTART study, we combine these three elements in a new stepped-care approach. The first step – the e-Health program – aims to develop and reinforce a positive cognition towards RTW through different modules tailored to the employee’s needs. With persistent sickness absence the program is followed by the second step – the PA – involving the workplace environment in a more substantial manner. Since the PA has shown to be more effective for employees with a positive cognition towards RTW and the aim of the e-Health program is to develop and reinforce such a positive cognition, the two interventions in the stepped-care approach complement each other.

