### Strengths and limitation

The 2 × 2 factorial design allows to test the main effects of the e-Health and PA separately, and the combined effect on lasting RTW, while keeping the sample size relatively small. A possible limitation of the 2 × 2 factorial design is that it requires both randomizations directly after baseline, but it is unknown how many employees eventually will complete PA, as this depends on persistent sickness absence of at least 6 weeks after baseline.

Another potential limitation of the current study could be non-adherence to the e-Health program. The e-Health program is mainly completed independently by the employee, and therefore relies more heavily on individual motivation. To minimize the chance of non-adherence employees will be stimulated to engage with the program [23] and are offered the possibility to have a 30 min consult with the OH practitioner. Furthermore, the patterns of app usage and adherence to the program will be investigated by means of the process evaluation.

The realist evaluation and the process evaluation will provide a deeper understanding of what elements are a success or failure, and why. This will provide important knowledge for further development and implementation of the stepped-care approach in practice.

The results from the effect- and process evaluations, together with perspectives from all stakeholders (employees, employers and OH practitioners), will provide a broad insight in the effectiveness of the stepped-care approach and its elements on lasting RTW for employees on sickness absence with psychological distress. These insights can be of large potential value to employees, employers and occupational practice.

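### The e-Health × PA interaction tests synergy, not whether the combination beats each intervention alone, and power for the combination question is well below the stated 80%

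*Protocol article*

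**What the plan says.** All references are to the protocol article.

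- **Data analysis.** The primary outcome is handled by Cox regression: "on lasting RTW a cox-regression will be conducted". Each intervention is assessed by pooling the two arms that contain it against the two that do not. On whether the combination "is superior to the separate interventions alone, we will study the interaction between PA and e-Health", no other analysis is named.
- **Discussion.** The hypothesis is that stepped care, that is "e-Health followed by PA, will be more effective on time to lasting RTW compared with usual care, and e-Health or PA only".
- **Randomization and blinding.** The design yields "two comparisons in the main outcome analysis: PA vs. not PA and e-Health vs. no e-Health". Both are pooled comparisons. No section describes a contrast of the combined arm with a single-intervention arm.
- **Sample size.** For the effect, "a hazard ratio (HR) was chosen of 1.8". With 80% power this "generated a total sample size of 144 participants, 36 participants per group". No effect size or power is given for the interaction or for the combined arm. The section does not say which comparison the 80% refers to, what share of participants will have an event, or whether the test is one- or two-sided. It prints alpha as 0.5.
- **Strengths and limitation.** The factorial design is credited with testing the separate effects "and the combined effect on lasting RTW, while keeping the sample size relatively small".

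**The concern.** In a Cox model the product term asks whether the HR of the combination differs from the product of the two separate HRs. Superiority over the separate interventions asks whether the combination has an HR above 1 against e-Health only, and also above 1 against PA only. These are different parameters, and their answers can differ in either direction.

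The practical risk lies in interpretation. A null interaction is what one expects when both components work independently, and that is a success for the combination. Read through the Data analysis sentence, the same result looks like failure to show superiority. Conversely, a positive interaction does not by itself show that the combination beats the better single arm. The test is also the least precise one available in a 2 × 2 design, and the Sample size section gives the reader no warning of this.

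**Working it through.** **1. What each test targets.** Write a for the log HR of e-Health only against usual care, b for PA only, and a + b + c for the combination, where c is the interaction.

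- Combined v e-Health only: b + c
- Combined v PA only: a + c
- Planned test: c

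Three cases:

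- Both HRs 1.8, c = 0. The combination has HR 1.8 × 1.8 = 3.24 against usual care and 1.8 against each single arm. The interaction is null.
- Both HRs 1.8, interaction ratio 0.8. The combination still beats each alone by 1.8 × 0.8 = 1.44, yet the interaction points the wrong way.
- HRs 0.7 (e-Health only), 1.5 (PA only) and 1.5 (both). The interaction ratio is 1.5 / (0.7 × 1.5) = 1.43, yet the combination equals PA alone. This is a logical counterexample; nothing in the article suggests that e-Health slows return to work.

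This step needs no assumed figure.

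**2. The stated sample size.** Inputs from the Sample size section: HR 1.8, power 80%, N = 144, 36 per group. Assumptions: alpha 0.05 (printed as 0.5), two-sided, equal allocation. The Schoenfeld formula for two equal groups gives

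D = 4 × (1.96 + 0.8416)² / (ln 1.8)² = 4 × 7.849 / 0.3455 = 90.9, so 91 events.

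That is 91/144 = 63% of participants (97 events, or 67%, by the Freedman formula). The article states no event share, so 144 is compatible with these inputs but not determined by them. Under these assumptions the 80% can only refer to a pooled 72 v 72 comparison. A combined-versus-single contrast contains 36 + 36 = 72 participants, who cannot supply 91 events.

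**3. Precision of the three kinds of test.** With D total events spread evenly over four arms:

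- pooled main effect: SE = 2/√D
- one combined-versus-single contrast: SE = 2/√(D/2)
- interaction: SE = 4/√D, four times the variance of a main effect

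Power = Φ(ln 1.8 / SE − 1.96), with ln 1.8 = 0.588. The two direct contrasts share the combined arm, so their correlation is 0.5, and power for both is the bivariate normal probability. The range runs from 91 events to 144, the case where every participant has an event.

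| | D = 91 | D = 117 | D = 144 |
|---|---|---|---|
| SE main / contrast / interaction | 0.210 / 0.296 / 0.419 | 0.185 / 0.261 / 0.370 | 0.167 / 0.236 / 0.333 |
| Pooled main effect, HR 1.8 | 80% | 89% | 94% |
| Interaction ratio 1.8 | 28.8% | 35.5% | 42.2% |
| One combined-v-single contrast, HR 1.8 | 51% | 61% | 70% |
| Both contrasts, HR 1.8 | 34% | 45% | 56% |
| Interaction ratio with 80% power | 3.24 | 2.82 | 2.54 |

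Smaller interactions fare worse: at a ratio of 1.5, power is 16% (D = 91) to 23% (D = 144). For 80% power at a ratio of 1.8, D = 16 × 7.849 / 0.3455 = 363.5, so 364 events, or 364 / (91/144) = 576 participants at the same event share.

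**The case against.** **The pooled main effects bear on the question.** If there is no interaction, they estimate exactly combined v PA only and combined v e-Health only, and with more precision. In a simulation with 36 per arm, HR 1.8 for each intervention, no interaction and 79% events, both pooled effects were significant in 78% of trials, against 48% for both direct contrasts. This stands. A reader might infer that nothing in the plan informs the hypothesis; that goes too far. The main effects carry the answer only on the no-interaction assumption, however, and the Data analysis section assigns the superiority question to the interaction instead.

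**Synergy is part of the rationale.** The Background and Discussion argue that e-Health builds the positive cognition on which PA depends. If each intervention alone had an HR near 1, the interaction ratio would equal the combined-versus-single HR. That is a good reason to estimate the interaction. It does not make the interaction a test of superiority in general, and even in that case it is the less precise estimate.

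**No decision rule is written.** A reader might infer that the plan will reject its hypothesis if the interaction is not significant. The article says only that the interaction will be studied. The risk is one of interpretation, not a stated rule.

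**A low rejection rate under no interaction proves nothing about power.** With a true null interaction, a two-sided 5% test should reject in about 5% of trials, half of them in the favourable direction, and simulation shows this. It illustrates that the target is wrong. The power figures are those in the table.

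**An analysis plan may hold the detail.** Any such plan is not shown. The sentence in the article nevertheless names a test that does not match its question, and a plan that follows it inherits the mismatch.

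**Conclusion.** The point holds. The interaction term does not test whether the combination is superior to e-Health only and to PA only, and the article names no analysis for that question that is valid without assuming no interaction. This conclusion rests on the model alone.

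The size of the power shortfall is conditional. With two-sided alpha 0.05, equal arms and 91 to 144 events among 144 participants, power is about 29–42% for an interaction ratio of 1.8, 51–70% for one direct contrast at HR 1.8, and 34–56% for both. A single figure of 29% would be too definite, because the article gives neither an event share nor sidedness and prints alpha as 0.5. Attaching the 80% to the pooled main effects is likewise an inference, since the Sample size section names no comparison; step 2 of the working shows why no other reading fits these assumptions.

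**What to change.** In Data analysis:

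- Fit one Cox model with e-Health, PA and their product. Test superiority over the separate interventions with two contrasts from it: combined v e-Health only (PA coefficient plus product coefficient) and combined v PA only (e-Health coefficient plus product coefficient).
- Claim superiority only if both are significant in the favourable direction. Because both must succeed, alpha need not be split.
- Report combined v usual care from the same model, since the Discussion hypothesis includes it.
- Keep the interaction, with its confidence interval, as the estimate of synergy, and say that a non-significant interaction is not evidence against superiority.
- Keep the two pooled comparisons as the main outcome analysis.

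In Sample size: state that the 80% power at HR 1.8 applies to the pooled main effects, give the assumed event share, alpha and sidedness, and report the lower power for the two contrasts and for the interaction.

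The cost is wording and analysis of data already being collected. The downside is that power for the combination question becomes visibly low: the contrasts correct the target but do not make the trial large enough for it. The change should be made before the allocation is unblinded, so that the contrasts are not chosen after the fact.
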